## Abstract

**Background:**

The coracoid approach is recognized as the simplest approach to perform brachial plexus anaesthesia, but needle visualization needs to be improved. With a different needle entry point, the retroclavicular approach confers a perpendicular angle between the ultrasound and the needle, which theoretically enhances needle visualization. This trial compares these two techniques. The leading hypothesis is that the retroclavicular approach is comparable to the infraclavicular coracoid approach in general aspects, but needle visualization is better with this novel approach.

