**Discussion:**

The conduct of this study will bring clear answers to our questions and, if our hypothesis is confirmed, will confer an anatomic alternative to difficult coracoid infraclavicular brachial blocks or could even become a standard for brachial plexus anaesthesia.

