Because a steep-angle needle-ultrasound (US) beam is often required, needle visualization remains a challenge in coracoid ICB, particularly when the needle approaches the neurovascular bundle [8, 9]. Because the needle entry point is different, the recently described retroclavicular (RCB) approach offers an almost perpendicular angle between needle and the US beam [10]. This technique has already been described as efficient, rapid, safe and simple to perform in both a recent study [11] and a recent case series [12]. As such, following the Standard protocol items: recommendation for interventional trials (SPIRIT) clinical trial design recommendations (see Additional file 1) [13], our hypothesis is that when comparing RCB with coracoid ICB for upper limb surgery, both techniques will offer similar outcomes except for needle visibility. We believe that the almost perpendicular needle-US beam angle in RCB will provide superior needle visibility to coracoid ICB.

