### Objectives

Our general objective is to make a formal comparison between RCB [10, 11] and coracoid ICB for brachial plexus anaesthesia. This study will delineate the differences between the two techniques. Our aim is to compare both techniques in terms of scanning time, needling time, total anaesthesia time, needle visibility, block needle passes, block success and early and late complications. We made the hypothesis that, while providing similar efficacy and better needle visualization than coracoid ICB, the time taken to perform RCB will not exceed the time taken to perform its comparator [3].

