#### Intervention – concomitant care

Strict adherence to protocol will be mandatory to allow inclusion of patients. Thus, if any other needle or any other local anaesthetics or other volume/dose of local anaesthetics are used, the patient will be excluded from the analysis.

If the patient received more than 2 mg of midazolam (or equivalent dose of other sedative drug) during the procedure, the patient will be included only if he is still able to adequately collaborate during the evaluation of motor and sensory blockade.

This means that patients maintain adequate response to verbal commands and remain competent after the medication administration. In any circumstances, if the drugs given exceed the allowed sedation as mentioned in this protocol (fentanyl 1 μg/kg, propofol 50 μg/kg/min), the plexus block will be considered a failure.

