##### Secondary outcome measures

Imaging time: will be measured in minutes and corresponds to the time interval between contact of the US probe with the patient skin and the acquisition of a satisfactory image.Needling time: will also be measured in minutes, from the start of the skin wheal to the removal of the block needle from the tissues.Sensory loss at 10, 20 and 30 minutes: will be assessed in the territory of the radial (lateral aspect of the dorsum of the hand), median (volar aspect of the index), ulnar (volar aspect of the fifth finger), musculocutaneous (lateral aspect of the forearm), and medial cutaneous nerve of the forearm (medial aspect of the forearm) distributions using a 3-point score, where 0 = normal sensation, 1 = diminished sensation to pinpricks (hypoesthesia), and 2 = loss of sensation to pinpricks (analgesia). The sum of five scores on a maximum of 10 will be the sensory-loss final score. An independent, blinded, research assistant will complete the sensory assessment at 10, 20 and 30 minutes.Motor block at 10, 20 and 30 minutes: motor function will be tested (0 = normal strength, 1 = weakness, 2 = paralysis) for the radial (wrist extension), median (thumb-fifth finger opposition), ulnar (fifth finger abduction), and musculocutaneous (elbow flexion) nerves. The sum of the four scores on a maximum of 8 will be the motor block final score. An independent, blinded, research assistant will complete the motor assessment at 10, 20 and 30 minutes.Success of plexus block: success is a dichotomic variable answered by yes or no. Success is defined as the completion of surgery without the need for additional LA infiltration, intravenous narcotics, or general anaesthesia. However, light sedation is allowed if deemed necessary by the anaesthesiologist. Light sedation includes midazolam 1 to 4 mg intravenously, fentanyl up to 1mcg/kg. A minimum sensory score of 9/10 will be necessary to proceed to surgery without additional LA infiltration. Patients with an overall sensory score under 9/10 at 30 min will be offered general anaesthesia or supplemental blocks.Total anaesthesia time: is measured in minutes and defined as the sum of performance time and time to achieve a minimum sensory score of 9/10. It is the time for readiness for surgery.Number of block needle passes: is defined as a unit of 1, 2, 3, etc., and is the number of times the block needle will have to be realigned on the skin in order to achieve its final positioning goal under the axillary artery.Needle visualization: procedures will be videotaped and reviewed simultaneously after study completion by 2 independent anaesthesiologists skilled in US-guided regional anaesthesia using a 5-point Likert scale to rate needle visibility (1 = very poor, 2 = poor, 3 = fair, 4 = good, 5 = very good). Needle visibility will be evaluated twice. First, for RCB, assessment will be made when the needle tip is seen 1 cm after crossing the clavicle acoustic shadowing. For the coracoid ICB, the first assessment will be at a needle tip depth of 1 cm. The second needle visibility assessment will be immediately before the local anaesthetic injection, when the visibility is theoretically optimized.Needle angle: using the same videotape that we used for the evaluation of the needle visibility, we will note the angle between the needle and the upper side of the ultrasound image. It will be a continuous outcome ranging from 0 to 90 degrees.Neurostimulation use: neurostimulation is accepted if needed. However, its use other than for a safety sentinel (defined by <0.3 mA) will be recorded for subsequent analysis. It will be a dichotomous outcome.Pain during the procedure: immediately after block completion, patients will be asked to rate their discomfort associated with the procedure using a 10-cm visual analogue scale (0 = no pain, 10 = worst pain imaginable) by an independent and blinded outcome assessor.Early and late complications: the incidence of needle-induced paresthesia, vascular puncture, Horner syndrome, dyspnea, and symptoms of LA toxicity will be noted. All patients will be contacted 48 hours after surgery to ask for any delayed complications, such as dyspnea, paresthesia, weaknesses, pain at the puncture site or haematoma. Patients with complications will be followed up by our research group and a consultation in neurology may be sought.

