#### Statistical methods

Analysis of the primary outcome: performance time will be analyzed with a non-inferiority test of the averages, with the objective of finding that the experimental RCB approach takes no longer to perform than the coracoid ICB approach.

The secondary outcomes will all be analyzed using superiority analysis. For continuous data or ordinal data with >8 categories, data will be compiled as average and standard deviation. If data are parametric, Student’s *t* test will be used and if not, the Mann-Whitney test will be used. For dichotomous data (block success, use of neurostimulation), the chi square or Fisher exact test will be used if n >5 or is not >5, respectively. Finally, for ordinal data the chi square test will be used if data are parametric, otherwise the Mann-Whitney test will be used.

Subgroup analysis will be conducted to evaluate if higher BMI influences the outcomes of performance time, needle visibility, number of needle passes and needle angle. Patients will be divided in two groups (of those with higher and those with lower BMI than the average BMI of all recruited patients) and analyzed according to their subgroup. If data are missing or if any patients drop out of the study, data will be analyzed using the intention-to-treat principle.

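### Similar efficacy is part of the hypothesis, but block success is tested only for superiority with no margin, so a non-significant result cannot support that secondary claim

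*Protocol article*

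**What the plan says.** The similarity hypothesis appears three times in the protocol article.

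- Abstract, Background: the leading hypothesis is that "the retroclavicular approach is comparable to the infraclavicular coracoid approach in general aspects", with better needle visualization.
- Background: "both techniques will offer similar outcomes except for needle visibility".
- Objectives: performance time is expected not to exceed that of the comparator "while providing similar efficacy and better needle visualization than coracoid ICB".

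The analysis is fixed under Statistical methods. Performance time gets a non-inferiority test of means. For everything else, "The secondary outcomes will all be analyzed using superiority analysis". Block success is named there as a dichotomous outcome for the chi-square or Fisher exact test. The only margin in the document is the 5% on performance time, under Sample size. The Discussion paragraph of the Abstract adds that, if the hypothesis is confirmed, RCB would offer an alternative for difficult coracoid blocks or "could even become a standard for brachial plexus anaesthesia".

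**The concern.** The hypothesis has three parts: time no longer, visibility better, efficacy similar. The first has a non-inferiority test and the second a superiority test, and each test suits its claim. The third has a superiority test, which answers a different question. If that test is significant, similarity is contradicted or RCB is better. If it is not, the trial has learned only that it could not separate the arms, and with about 50 patients per arm that can happen when RCB is materially worse.

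At stake is one secondary conclusion. A faster block that fails more often would be a poor candidate for a new standard. Under the Success of plexus block definition, a patient scoring below 9/10 at 30 minutes is offered general anaesthesia or supplemental blocks. A report that success did not differ significantly could be taken as confirming the efficacy part of the hypothesis, and nothing in the stated analysis guards against that.

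This is not a detail left to an unseen analysis plan. The protocol positively assigns superiority to all secondary outcomes and names block success.

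**Working it through.** **1. What the planned sample size covers.** Inputs from Sample size: ICB mean 5 min 36 s = 336 s; RCB mean as stated 4 min 29 s = 269 s; SD 2 min 18 s = 138 s; margin 5% of 336 = 16.8 s; one-sided alpha 0.05; power 0.90.

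n per arm = 2 × (1.645 + 1.282)² × 138² / (16.8 + 67)² = 46.4, so 47. The t-based version gives 48. Both are within two patients of the stated 49, which therefore belongs to performance time alone. No success rate, margin or power is given for block success.

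**2. A result that would read as no significant difference.** Assumed: 49 per arm, a two-sided 5% test (no level is stated for secondary outcomes), ICB 44/49 = 89.8%, RCB 37/49 = 75.5%, difference -14.3 points.

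- Chi-square without continuity correction: pooled rate 81/98 = 0.8265; statistic = 0.1429² / (0.8265 × 0.1735 × 2/49) = 3.49; p = 0.062. Fisher exact p = 0.108.
- Newcombe 95% interval: the Wilson limits are 0.782 to 0.956 (ICB) and 0.619 to 0.854 (RCB). Lower limit = -0.1429 - √[(0.7551 - 0.6191)² + (0.9556 - 0.8980)²] = -0.291. Upper limit = -0.1429 + √[(0.8540 - 0.7551)² + (0.8980 - 0.7824)²] = +0.009.

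This is the boundary: at 36/49 the chi-square test becomes significant (p = 0.037; Fisher 0.066), and at 35/49 both do (0.021; 0.039). With 55 per arm, 50/55 against 43/55 behaves alike: p = 0.065 and 0.112, interval -26.3 to +1.0 points.

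**3. How often a real deficit would be missed.** Assumed true rates 90% (ICB) and 80% (RCB). By exact enumeration, power is 30% (chi-square) or 19% (Fisher) at 49 per arm, and 31% or 22% at 55. Roughly 70-80% of such trials would find no significant difference.

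**4. Precision available.** Half-width of the 95% interval = 1.96 × √(2p(1-p)/n). At p = 0.90 this is 11.9 points for n = 49 and 11.2 for n = 55. Over p = 0.85 to 0.95 and both sizes it runs from 14.1 down to 8.1 points.

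**5. Chance of meeting a margin when the arms are truly equal.** Exact enumeration, both true rates 90%, lower Newcombe limit above minus the margin. Margins are illustrative.

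| Margin | 95% interval, n = 49 / 55 | One-sided 0.05 (90% interval), n = 49 / 55 |
|---|---|---|
| 10 points | 33% / 37% | 49% / 51% |
| 15 points | 65% / 70% | 77% / 82% |

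With the 95% interval and true rates between 85% and 95%, the 10-point margin is met in 27% to 51% of trials and the 15-point margin in 54% to 87%.

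**The case against.** The best defence is that the error has not been made yet. The protocol names tests; it nowhere says that a non-significant result will be read as similarity. The confirmatory question is performance time, similar efficacy is a subordinate clause in the Objectives, and the same section says the study will delineate differences, for which superiority tests are natural. Leaving an unpowered secondary outcome without a margin is ordinary practice. The numerical example sits at the edge of significance: if both true rates were 90%, RCB would fall seven or more successes behind in only about 1.4% of trials.

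Most of this stands, and it limits the point without removing it. The efficacy claim is also in what the Abstract calls the leading hypothesis, and no planned analysis can confirm it.

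Three stronger readings are tempting, and the documents support none of them.

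- A reader might infer that the main conclusion is undermined. It is not: performance time has its own margin and sample size.
- A reader might infer that RCB is expected to lose about 14 points of success. The protocol gives no rate; Data monitoring says only that the feasibility study found similar success.
- A reader might infer that the sedation rules behind the success definition conflict. The success definition says "Light sedation includes midazolam 1 to 4 mg intravenously, fentanyl up to 1mcg/kg", while the failure rule under concomitant care applies "if the drugs given exceed the allowed sedation as mentioned in this protocol" and lists fentanyl and propofol. These are incomplete cross-references. Merging them would mean clinical choices about propofol and high-dose midazolam, and no usage rates are given to show that any patient would be affected.

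**Conclusion.** The point holds for a secondary claim. The stated superiority analysis of block success can show a difference but cannot support the similar-efficacy part of the hypothesis. On assumed rates, an observed deficit of 14 points with an interval reaching -29 would be non-significant at 49 per arm, and a true 10-point deficit from 90% would be missed in about 70-80% of trials. The inference does not depend on these figures, but its practical size does, since every success rate and margin used is an assumption. The correction is worth making because it costs almost nothing and settles what the trial may say about efficacy.

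**What to change.** Add to Statistical methods, in substance: block success will be reported as the risk difference (RCB minus ICB) with its confidence interval; a non-significant superiority test will not be read as similar efficacy; similar efficacy will be claimed only if the lower limit excludes a margin of [x] points, set by the clinical team before anyone sees success by arm; otherwise the report will say only that no difference was detected.

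State the interval level too. Sample size mentions both a 95% interval and a one-sided 0.05, and the chance of meeting a margin differs between them. The margin should be fixed promptly, because the statistician is not blinded (Blinding) and a quarter of the calculated sample has been recruited (Trial status).

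The cost is a few sentences and one clinical decision, with no new patients, visits or data. The downside is that the claim may well fail at this size even if the blocks are equally effective. If the team finds no defensible margin, it can make no similarity claim and report the interval alone. The sedation lists and the other outcome definitions need no change for this point.

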#### Sample size

We decided to conduct a non-inferiority trial with the aim of demonstrating that performance time for the RCB approach is no longer than for the coracoid ICB approach. On the basis of a recent study [15], we established that the performance time for the coracoid ICB approach is 5 min 36 s, with 45 s of visualization time. On the basis of the feasibility trial recently conducted, needling time for the RCB approach is 3 min 42 s [11]. If we use the same imaging time of 45 s, we expect a performance time of 4 min 29 sec for the experimental approach. The standard deviation used for both groups was 2 min 18 s, as reported in the literature [15]. We deemed that a time superiority of 5% would be significant. In other words, RCB performance time will be deemed non-inferior to ICB if the upper margin of the 95% confidence interval created around RCB performance time is under the ICB performance time plus 5%. When using these hypotheses to conduct a non-inferiority analysis, a calculated sample size of 49 patients per group will be required to provide statistical power of 0.90 and one-sided type I error of 0.05. To compensate for potential dropouts or inadequate procedures, we will aim for a sample size of 55 patients per group.

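### The test for ordinal outcomes with eight or fewer categories turns on an undefined parametric criterion, so needle visibility could be tested with a chi-square that ignores grade order

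*Protocol article*

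**What the plan says.** All quotes in this field are from the protocol article.

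- **Ordinal rule (Statistical methods).** "for ordinal data the chi square test will be used if data are parametric, otherwise the Mann-Whitney test will be used". The text does not define parametric for an ordinal score.
- **Rule for longer scales (Statistical methods).** "For continuous data or ordinal data with >8 categories, data will be compiled as average and standard deviation". These outcomes then go to Student's t test or Mann-Whitney.
- **Framework (Statistical methods).** "The secondary outcomes will all be analyzed using superiority analysis".
- **Needle visibility (Secondary outcome measures).** Videos are "reviewed simultaneously after study completion by 2 independent anaesthesiologists", "using a 5-point Likert scale to rate needle visibility", at two points in the procedure. The text shown does not say how the two ratings are combined.
- **Hypothesis (Abstract, Background).** The two approaches are expected to be comparable in general, but "needle visualization is better with this novel approach". The main Background section repeats this.
- **Blinding.** The authors did not consider it necessary to blind the statistician.
- **Binary outcomes (Statistical methods).** "the chi square or Fisher exact test will be used if n >5 or is not >5, respectively". The symbol n is not defined.

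**The concern.** The ordinal sentence appears to carry over the t test/Mann-Whitney switch given just before it for continuous data, with chi-square put in place of the t test. That substitution does not work. A five-grade score has no parametric state that would make chi-square appropriate. Pearson chi-square on a 2×5 table treats the grades as unordered labels, so it asks whether the two distributions differ in any way. The hypothesis is that visibility is better, which is a question about order and direction.

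Two things are at stake for an outcome that is formally secondary but central to the trial's rationale. First, a reader cannot tell from the protocol which test will be run, and a statistician who knows the allocation would settle it after seeing the data. Second, if chi-square is chosen, its four degrees of freedom spread the power over patterns nobody is interested in, and a significant result need not mean that visibility improved.

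**Working it through.** **1. Which outcomes the sentence governs.** The sensory score runs 0-10 (11 values) and the motor score 0-8 (9 values). Both exceed eight categories and go to the t test/Mann-Whitney rule. A single visibility rating has 5 values and falls under the ordinal sentence. The mean of two raters can be 1, 1.5, …, 5, which is 9 values. Their sum, 2 to 10, also has 9. Either would move visibility to the other rule. As written, then, chi-square, Mann-Whitney and the t test can all be reached for this one outcome.

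**2. The plan's own figure.** The only sample-size figure is for performance time. With SD 138 s, margin 5% of 336 s = 16.8 s and expected difference 269 − 336 = −67 s, at one-sided 0.05 and power 0.90:

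n = 2 × (1.645 + 1.282)² × 138² / (16.8 + 67)² ≈ 47 per group (48 with the t distribution)

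This is close to the stated 49; and 49/0.90 = 54.4, hence 55. The protocol gives no power, effect size or grade distribution for visibility, so there is nothing to reproduce for that outcome.

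**3. Power under assumed ordered shifts.** The inputs below are assumptions, except for the group sizes of 49 and 55.

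- Five control distributions over grades 1-5 (%): 10/20/40/20/10, 20/20/20/20/20, 5/10/20/35/30, 20/30/30/15/5 and 2/8/30/40/20.
- RCB arm: odds of grade k or higher = OR × the same odds under ICB. Example: with 10% at grade 5 and OR 2, the odds are 2 × 0.10/0.90 = 0.222, giving 18.2% at grade 5.
- Two-sided 0.05, 100,000 simulated trials per scenario, Pearson chi-square against tie-corrected Mann-Whitney.
- Relative loss = (Mann-Whitney power − chi-square power) / Mann-Whitney power.

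Results at 55 per arm, range over the five distributions:

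| OR | Mann-Whitney | Chi-square | Relative loss |
|---|---|---|---|
| 1.5 | 21-22% | 11-13% | 42-46% |
| 2 | 50-53% | 29-33% | 38-41% |
| 2.5 | 73-76% | 50-54% | 29-32% |
| 3 | 87-89% | 67-72% | 20-22% |
| 4 | 97-98% | 88-91% | 7-10% |
| 6 | over 99% | 98-99% | 1-2% |

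Worked line (uniform control, OR 2.5): (0.762 − 0.543)/0.762 = 0.29. At 49 per arm the loss runs from 41-47% at OR 1.5, through 32-35% at OR 2.5, to 2-3% at OR 6.

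**4. Analytic check.** Take the same noncentrality on 1 df and on 4 df. For 80% power on 1 df it is (1.960 + 0.842)² = 7.85, and on 4 df this gives 60%. Powers of 70, 80 and 90% become 48, 60 and 74%, relative losses of 31, 26 and 18%. This agrees with the simulation.

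**5. Type I error.** With no difference between arms, chi-square rejects in 4.0-5.0% of trials, at or below nominal.

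**6. A change that is not an upward shift.** Assume control 5/10/20/35/30 and RCB 30/15/10/15/30, at 55 per arm. Chi-square power is 95%, Mann-Whitney 60%. The control mean grade is 0.05 + 0.20 + 0.60 + 1.40 + 1.50 = 3.75, and the RCB mean is 0.30 + 0.30 + 0.30 + 0.60 + 1.50 = 3.00. Chi-square is more sensitive here, but to a pattern in which average visibility is lower with RCB.

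**7. The n > 5 rule.** If n meant group size, 49 or 55 always exceeds 5 and Fisher's test would never be used. Expected failures per arm fall below 5 when the pooled failure rate is under 5/55 = 9.1% to 5/49 = 10.2%. At an assumed 95% success rate, which is not in the protocol, they would be 0.05 × 49 = 2.45 to 0.05 × 55 = 2.75.

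**The case against.** The strongest reply is that a five-grade score would usually be judged non-parametric, and the same sentence then gives Mann-Whitney, the test one would ask for. That stands. A reader might infer that the plan commits visibility to chi-square; the text supports only that it could. If the raters' scores are averaged and nine values count as more than eight categories, chi-square is not reached at all.

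A reader might also infer that the trial loses about a third of its power for visibility. The protocol supplies nothing from which to derive that. A third is what one assumed odds ratio near 2.5 produces, and the loss is much larger or close to nil at others.

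Nor is the chi-square test itself invalid: taken alone it holds its type I error. The selection criterion is what is unsound, and that reassurance does not extend to choosing between tests after seeing the data.

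It would also be too strong to call visibility the only expected advantage, since the Risk of bias section reports that the consent form mentions an expected shorter and less painful block. That section also advises caution with the Likert results because the scale is unvalidated.

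Finally, n > 5 may well be shorthand for a cell-count rule, because a rule that names Fisher's test presumably intends its use at times. That part is a clarification only.

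What survives is that the stated rule is wrong as written. It is not a detail left to a fuller document.

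**Conclusion.** The concern holds in limited form. The protocol selects the test for short ordinal scales by a criterion with no meaning for them, and one branch leads to a test that disregards order and direction. The test for needle visibility is therefore not fixed in advance.

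The cost is conditional on two things: chi-square being the test chosen, and the true effect being an ordered shift. Given both, the relative power loss across the assumed scenarios at both group sizes runs from about 1% to 47%. It is largest for modest effects. Where Mann-Whitney would have 80-90% power, it is about a fifth to a quarter. These figures rest on the assumed grade distributions, proportional odds and a two-sided 0.05 level, none of which the protocol states for this outcome.

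Visibility is a secondary outcome, and the non-inferiority conclusion on performance time is unaffected. The point is worth correcting because the outcome carries the trial's main superiority claim.

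**What to change.** Replace the ordinal sentence under Statistical methods with: *Ordinal outcomes will be compared with the Mann-Whitney test (or a proportional-odds model), with no data-dependent switch.* Choose one of the two when writing it. State that it applies to needle visibility at both assessments, whether the two raters' scores are analysed singly or averaged, so that the nine-value average does not slip into the rule for more than eight categories.

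As a minor clarification, replace the n > 5 wording with: *Fisher's exact test will be used when any expected cell count is below 5.*

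Accounting for site in the ordinal analysis is optional and does not follow from this error.

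The cost is wording only, with no change to sample size, conduct or data collection. Because the videos are to be rated after study completion, the rule can be settled before any visibility ratings exist.

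### The BMI subgroup analysis splits patients at the sample mean and names no treatment-by-BMI interaction test, so as written it does not test whether BMI alters the RCB–ICB difference

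*Protocol article*

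**What the plan says.** The last paragraph of Statistical methods in the protocol article sets the question: "Subgroup analysis will be conducted to evaluate if higher BMI influences the outcomes of performance time, needle visibility, number of needle passes and needle angle". It then gives the method: "Patients will be divided in two groups (of those with higher and those with lower BMI than the average BMI of all recruited patients"), after which patients are to be "and analyzed according to their subgroup".

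The tests named earlier in that section are a non-inferiority test of means for performance time and, for the secondary outcomes, Student's t, Mann-Whitney, chi-square and Fisher's exact tests. All of them compare two groups. The section names neither an interaction term nor any analysis of BMI on its continuous scale. It also does not say outright that each half gets its own test or that the two verdicts will be compared.

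**The concern.** The trial exists to compare RCB with ICB, so the useful BMI question is whether the difference between the techniques changes with BMI. The stated method does not answer it on either available reading.

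- **RCB against ICB within each half, verdicts contrasted.** One half passing and the other failing is not evidence that BMI matters. Each half has about half the patients, so the verdicts often differ by chance.
- **High-BMI against low-BMI patients.** This shows whether heavier patients have longer times or poorer views whichever technique is used. It does not show whether BMI alters the comparison.

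On both readings, cutting a continuous covariate at its mean discards information. What is at stake is an unfounded statement that one technique suits only lighter or only heavier patients, or a real modification that goes unnoticed.

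**Working it through.** **Inputs (protocol, Sample size).** ICB mean: "the performance time for the coracoid ICB approach is 5 min 36 s", i.e. 336 s. RCB mean 4 min 29 s = 269 s. SD 2 min 18 s = 138 s in both groups. Margin 5% of 336 s = 16.8 s. The error rates are "statistical power of 0.90 and one-sided type I error of 0.05". Numbers: "a calculated sample size of 49 patients per group will be required", and for recruitment "we will aim for a sample size of 55 patients per group".

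**1. The plan's own figure.** Distance from the expected difference to the margin: 16.8 + (336 − 269) = 83.8 s.

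n per group = 2 × 138² × (1.645 + 1.282)² / 83.8² ≈ 46.5, so 47 (48 with the noncentral t). This is within two patients of the stated 49, so the inputs are read correctly. One-sided 0.025 would give 57 and does not reproduce it.

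**2. Verdicts in the two halves when BMI has no modifying effect.** Assume equal halves and the same true difference in each.

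| | 49 per arm | 55 per arm |
|---|---|---|
| Patients per arm in each half, h | 24.5 | 27.5 |
| SE = 138 × √(2/h) | 39.4 s | 37.2 s |
| 83.8 / SE | 2.13 | 2.25 |
| Power per half, p = Φ(83.8/SE − 1.645) | 0.685 | 0.728 |
| Exactly one half passes, 2p(1 − p) | 2 × 0.685 × 0.315 = 43% | 2 × 0.728 × 0.272 = 40% |

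A simulation of 20,000 trials, splitting at the sample mean of a skewed BMI (log-normal, assumed), gave 45% and 41%.

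**3. How far this depends on the size of the effect.** For non-inferiority with a true difference of 0, disagreement is 20–21%. For a superiority outcome at two-sided 0.05 (alpha assumed; none is stated for secondary outcomes), it depends on overall power:

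| Overall power | Halves disagree |
|---|---|
| no treatment effect | 9.5% |
| 80% | 50% |
| 90% | 47% |
| 95% | 40% |
| 99% | 24% |
| 99.9% | 10% |

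**4. An interaction test instead.** In the same simulation, a test of the difference between the two halves' effects at two-sided 0.05 gave a false BMI finding in 4.9% of trials at both sample sizes.

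Its power is limited. SE of the difference between halves = 138 × √(4/h) = 55.8 s at 49 per arm and 52.6 s at 55. For a 67 s difference, power = Φ(67/55.8 − 1.96) = 22%, or 25% at 55 per arm. The difference detectable with 80% power is 2.80 × SE, about 156 s or 147 s.

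**5. Cost of the split.** The slopes below are illustrative assumptions; the protocol gives none. BMI is taken as normal, with 49 per arm. The SE of the slope with continuous BMI is 138 / √(98 × 0.25) = 27.9 s per SD. The mean split turns a slope s into a between-half difference of about 1.6 × s, tested against an SE of 55.8 s.

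| Assumed slope | Difference between halves | Power, continuous BMI (simulated) | Power, mean split (simulated) |
|---|---|---|---|
| 42 s per SD | about 67 s | 30% | 21% |
| 60 s per SD | about 96 s | 54% | 38% |
| 80 s per SD | about 128 s | 79% | 59% |

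**The case against.** The strongest reply is that the charge rests on inference. The article does not state separate tests in each half, does not say that verdicts will be contrasted, and can be read as a comparison of heavier with lighter patients, where disagreement between halves cannot arise. That stands as a limit on the 40–43% figure, which applies only to the first reading. It does not rescue the method, because the second reading leaves effect modification untested.

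A second reply is that this is a condensed article and the analysis plan, which is not shown, may specify an interaction. That also stands: one can say only that none is named. But the article does more than stay silent, since it fixes the split, the cut point and analysis by subgroup.

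A reader might infer that the halves would disagree about half the time whatever the outcome. The documents do not support that. A figure of 48% arises on performance time only with a two-sided superiority test (power per half 0.397; 2 × 0.397 × 0.603 = 0.479), whereas the plan analyses that outcome by non-inferiority. Disagreement is also much rarer when the treatment effect is nil or very large. The latter is plausible for needle angle, given the near-perpendicular approach described in the Background.

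A reader might also infer that a cut known only after recruitment introduces bias. It does not: the rule is set in advance and uses only a baseline covariate. The objection to it is loss of information.

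Finally, the proposed test has low power too. At 42 s per SD, equivalent to a between-half difference as large as the whole expected treatment effect, it reaches only about 30%. That is a reason to call the analysis exploratory, not a reason to keep the split.

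**Conclusion.** The point holds in this form: the stated method does not test whether BMI modifies the RCB–ICB difference, and it uses BMI inefficiently. If verdicts in the two halves are contrasted, they disagree on performance time in about 40–43% of trials at the plan's design values with no modification present, against about 5% false findings with an interaction test. That figure assumes equal halves, the same true difference of 67 s in each, and the planned non-inferiority test at one-sided 0.05. No such figure can be computed for visibility, needle passes or angle, because the article gives no expected effects for them.

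The loss of power from the split is 9 to 20 percentage points over the assumed slopes (30 − 21 = 9; 54 − 38 = 16; 79 − 59 = 20). The direction is firm, while the size depends on slopes that are not from the protocol. The primary conclusion, the sample size and the randomisation are not affected.

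**What to change.** Replace the last part of the subgroup paragraph with wording such as: for performance time, needle visibility, number of needle passes and needle angle, modification of the RCB–ICB difference by BMI will be assessed with a treatment-by-BMI interaction, BMI entered as a continuous variable. The interaction will be reported with its 95% confidence interval. Results above and below the mean BMI will be shown descriptively only. The analysis is exploratory, because power for an interaction is low at this sample size.

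The model should suit each outcome, for example linear for time and angle, ordinal for visibility and a count model for passes.

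The cost is small. BMI must already be recorded to form the planned split, and no extra patients or visits are needed. The downsides are slightly more modelling work and an assumed, for instance linear, form for BMI. The wording should be settled before the data are analysed; when the article was submitted, one fourth of the calculated sample had been recruited and no interim analysis was planned.
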